## Abstract

**Background:**

The seasonal influenza vaccine is less effective in older people and a single dose is unlikely to provide the year-round protection necessary for tropical climates which have year-round influenza virus activity. This study aims to assess the effect of a trivalent inactivated influenza vaccine (IIV3) booster at 180 days on haemagglutination-inhibition (HI) antibody titres for each of the influenza strains present in the administered vaccine in older people aged 65 years or above in Singapore.

**Methods/design:**

This is a single-centre, randomised, observer-blind, active-comparator controlled, parallel-group, phase IV trial in 200 adults aged 65 years or older. Study participants will be assigned to one of two groups in a 1:1 ratio and followed for 1 year, with five scheduled visits. The control group will receive IIV3 at day 1, and an active comparator (Tetanus-diphtheria-pertussis vaccine) at day 180. Participants in the experimental group will receive IIV3 containing the same strains at day 1 and day 180. Endpoints are immunological, and include measures of HI titres, microneutralisation titres (MN) and cell-mediated immunity from first vaccination up to day 360.

**Discussion:**

If superiority of 6-monthly influenza vaccination is demonstrated, this study could form the basis for a larger clinical trial with influenza infection as the primary endpoint.

**Trial registration:**

ClinicalTrials.gov, ID: NCT02655874. Registered on 12 January 2016.

**Electronic supplementary material:**

The online version of this article (doi:10.1186/s13063-017-1808-8) contains supplementary material, which is available to authorized users.

## Background

Influenza is popularly characterised as an infection acquired during the cold, winter months in temperate climates. Tropical and subtropical countries also have a significant burden of disease from influenza but the epidemiology is much more variable [1, 2]. This includes multiple annual influenza seasons and year-round virus activity [3, 4]. The implications of this for influenza vaccination schedules have not been tested in randomised clinical trials but are likely to be important in older people and in other populations with impaired vaccine responses.

Year-round influenza virus activity implies that an effective vaccine must also provide year-round protection. However, the duration of protection provided by the influenza vaccine has not been well established. No clinical studies of vaccine efficacy or effectiveness are available from countries with year-round influenza activity, but over the course of a single winter season declining vaccine effectiveness has been reported from test-negative case control studies in Europe and Australia [5–7]. For example, in Spain vaccine effectiveness was 61% (95% CI 5 to 84) in the first 100 days after vaccination, 42% (95% CI −39 to 75) between 100 and 119 days, and 0% thereafter. This decline in effectiveness mainly affected older people aged over 65 years [6].

In response to these reports, the I-MOVE multicentre, test-negative, case-control study reviewed data collected from more than 11,000 seasonal influenza infections over 2010–2015 in eight European countries [8]. Vaccine effectiveness against influenza A/H3N2 and B infection declined across all age groups as the winter season progressed. This decline was most marked in older people, with little vaccine effectiveness evident by day 140 (subtype A/H3N2) or day 200 (influenza B). Surprisingly, vaccine effectiveness appeared to be maintained (over 200 days) for subtype A/H1N1. The authors hypothesise that this may reflect the homogeneity of the A/H1N1 strain (pdm2009) across the period of the study, with repeated vaccination (or infections) boosting strain-specific antibody titres.

As an alternative to clinical effectiveness, the trajectory of immune responses after vaccination can be used to estimate the duration of protection. The haemagglutination inhibition (HI) titre is the major immune correlate of protection, and is used by regulatory agencies, such as the Food and Drug Administration (FDA) and the European Medicines Agency (EMA), for influenza vaccine licensing. A titre ≥1:40 is estimated to offer 50% protection against infection, and this threshold is conventionally labelled as ‘seroprotection’ [9]. A systematic review of vaccine antibody persistence studies, performed by the study team in preparation for this trial, suggested that in older people there is a steady decline in HI titres, and at between 180 and 360 days titres return to the pre-vaccination level [10]. Studies have identified increasing age and lower pre-existing HI titres as predicting reduced duration of antibody persistence, while the impact of comorbidities, such as diabetes, on persistence is less clear [11, 12].

### Primary objective

The study aims to assess the effect of a trivalent inactivated influenza vaccine (IIV3) booster at 180 days on HI antibody titres for each of the influenza strains present in the administered vaccine in adults, aged 65 years and older.

### Secondary objectives

To compare the antibody response (HI and microneutralisation (MN) titres) at 360 days after IIV3 and IIV3 + boosterTo compare the immune response between primary and booster IIV3 vaccinationTo assess the safety of an IIV3 booster at 180 days

We hypothesise a booster injection of seasonal IIV3 at 180 days after primary vaccination improves year-round seroprotection against influenza infection in older people aged 65 years and above.

## Methods/design

### Summary of study design

This is a single-centre, randomised, observer-blind, active-comparator controlled, parallel-group, phase IV trial in 200 adults aged 65 years or older. Each study participant who meets eligibility criteria and signs the Informed Consent Form will be allocated to one of two groups in a 1:1 ratio (Fig. 1). Participants will be followed for 1 year, with five scheduled visits. All participants will provide blood samples for immunogenicity assessment at days 1 (pre-injection), 28, 180 (pre-injection), 208, and 360 (Fig. 2).

**Fig. 1 Fig1:**
[figure not shown]
Stratified randomisation by age at enrolment day 1

**Fig. 2 Fig2:**

Study timeline from day 1 (D1) to day 360 (D360)

Solicited and unsolicited adverse events (AEs) will be collected for all participants for 7 days after each vaccination. All serious adverse events (SAEs) will be collected for 28 days after each vaccination. SAEs that are considered related to vaccination and/or study procedures will be monitored until resolution or stable. Participants will also be contacted 2-weekly as surveillance for clinical endpoints, including influenza-like illnesses (ILI) and polymerase chain reaction (PCR)-confirmed influenza.

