### Participant withdrawal

Participants will be informed that they have the right to withdraw from the trial at any time. Participants who are withdrawn will not be replaced. If withdrawal occurs within 28 days after vaccination, and if agreeable, the participant will continue to be contacted by telephone at expected visits to confirm AE or SAE status.

The investigator will discontinue vaccination if the participant experiences any SAE related to the administration of the previous vaccine, including an anaphylactic or other significant allergic reaction. In addition, a participant may be withdrawn from the study if, in the investigator’s judgement, there are safety concerns, or significant noncompliance with the study protocol. If a participant experiences an AE or SAE considered by the investigator to be related to vaccination, the participant will be followed until the condition resolves or becomes stable.

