### Safety assessment methods

To ensure participants’ safety, there will be an immediate post-vaccination surveillance period. Participants will be kept under observation for 15 min after each vaccination. AEs will not be actively solicited during this surveillance period. To collect solicited AEs, all participants will be provided with a safety diary card, a digital thermometer, and a flexible ruler and will be instructed how to use them. The following items will be recorded in the diary card on the day of vaccination and for the next 6 days or until resolution: daily temperature with the route by which it was taken; daily measurement or intensity grade of all other solicited injection site and systemic reactions; action taken for each event (e.g. medication), if any. To collect unsolicited AEs, all participants will be instructed to record any unsolicited AEs that may occur for 7 days after each vaccination. Space will be provided in the diary card for this purpose. AEs which are likely to be related to trial products, whether serious or not, will be followed up by the investigator until their complete disappearance or stabilisation. Information on all SAEs and UPIRTSO events will be collected and assessed throughout the trial, from enrolment until the final study visit (day 360).

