### Safety monitoring plan

All vaccines used in this study are part of routine vaccination schedules. Safety data has been established from millions of administered doses. According to the WHO, the incidence of vaccine-related SAEs, such as anaphylaxis and GBS, is approximately 1 per million doses. The rate of mild, nonsevere AEs in clinical trials is similar between influenza vaccine and placebo. Vaccine-related SAEs are not expected in a clinical trial of this size. AEs will be monitored for the first 7 days after each vaccination. SAEs will be monitored for the first 28 days after each vaccination. An interim safety analysis will not be performed. The study team will review any UPIRTSO events and stop the trial if significant risk to participants from continuing in the trial is suspected.

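### SAE collection is set at 28 days after each vaccination in two places but at enrolment to day 360 in a third, and the SAE outcome spans days 1 to 360

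*Protocol article*

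**What the plan says.** Two places in the protocol article set a 28-day period:

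- Summary of study design, text under Fig. 2: "All serious adverse events (SAEs) will be collected for 28 days after each vaccination". The next sentence covers follow-up of known events separately: "SAEs that are considered related to vaccination and/or study procedures will be monitored until resolution or stable".
- Safety monitoring plan: "SAEs will be monitored for the first 28 days after each vaccination".

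Participant withdrawal uses the same 28 days for safety contact after a participant leaves: "If withdrawal occurs within 28 days after vaccination, and if agreeable, the participant will continue to be contacted by telephone".

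One place sets a full-trial period. Safety assessment methods states: "Information on all SAEs and UPIRTSO events will be collected and assessed throughout the trial, from enrolment until the final study visit (day 360").

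The last item under Secondary outcomes is the share of participants who have an SAE between day 1 and day 360. It defines an outcome and is not a collection rule, but its period fits only the full-trial rule.

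Both groups are injected twice, on days 1 and 180. For the control group: "The control group will receive IIV3 at day 1, and an active comparator (Tetanus-diphtheria-pertussis vaccine) at day 180". On follow-up: "Participants will be followed for 1 year, with five scheduled visits".

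**The concern.** An outcome that runs from day 1 to day 360 needs SAE collection over the same period. Site staff who work from the design summary or the monitoring plan would stop recording new SAEs 28 days after each injection. Staff who work from the safety methods would record them to the final visit.

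If the shorter rule is followed, the reported figure would be labelled as one-year SAE incidence but would hold only events from two short windows. If practice varies, capture between and after the windows would be uneven. Neither can be repaired at analysis, because an SAE that was never recorded cannot be recovered. Nor can an analysis plan settle it, since the question is what is collected at the site. Safety of the day-180 booster is a stated secondary objective, and the Discussion notes that data on 6-monthly vaccination are lacking, so the SAE figure will be read with some care.

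**Working it through.** The plan gives no figure to reproduce on this point. The check has three parts: whether the statements can be reconciled, how much of the outcome period the 28-day rule covers, and what that could do to the reported percentage.

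**1. Can the statements be reconciled?**

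| Section | Events covered | Period |
|---|---|---|
| Summary of study design (Fig. 2 text) | all SAEs, collected | 28 days after each vaccination |
| Safety monitoring plan | SAEs, monitored | first 28 days after each vaccination |
| Safety assessment methods | all SAEs, collected and assessed | enrolment to day 360 |
| Secondary outcomes | participants with an SAE | day 1 to day 360 |

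- A split by type of SAE (all for 28 days, a subset to day 360) fails, because both collection rules say all SAEs.
- A split between new events and follow-up of known ones fails, because the Fig. 2 text speaks of collection and handles follow-up of related SAEs in its own sentence.
- A single slip is unlikely, because the 28-day period appears twice and the withdrawal rule is tied to it.

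**2. Days covered by the 28-day rule**

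Inputs: injections on days 1 and 180 (Abstract, Methods/design); 28 days after each (Fig. 2 text); outcome period of 360 days (Secondary outcomes).

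- Counting the injection day as the first of the 28: days 1–28 and 180–207, so 2 × 28 = 56 days. 56/360 = 15.6% covered; 360 − 56 = 304 days, or 84.4%, not covered.
- Counting the injection day in addition: days 1–29 and 180–208, so 2 × 29 = 58 days. 58/360 = 16.1% covered; 302 days, or 83.9%, not covered.
- Under the enrolment-to-day-360 rule: 360/360 = 100% covered.

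**3. Illustration of the undercount**

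The article gives no expected SAE rate. Assume a constant hazard and a 360-day risk p of 5%, 10% or 20%. The share of participants with an SAE inside 56 days is 1 − (1 − p)^(56/360).

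| Assumed 360-day risk | Recorded within the windows | Recorded ÷ true |
|---|---|---|
| 5% | 0.8% | 15.9% |
| 10% | 1.6% | 16.3% |
| 20% | 3.4% | 17.1% |

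This assumes that the 28-day rule is applied strictly and that no SAE enters the record by another route.

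**The case against.** The best reply is that the loss may never happen. Safety assessment methods is the dedicated section on SAE collection and its period matches the outcome, so it may well be the rule in use. Neither 28-day statement says that collection stops there, and collecting to day 360 includes both windows. This stands in part: staff who collect to day 360 satisfy the literal words of all the sections. But a stated 28-day period reads naturally as a limit, and the article never says otherwise.

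A second reply is that other routes would find many of the events. Influenza surveillance has contact every two weeks to day 360 and asks about hospitalisations. Hospitalisations and all-cause mortality are outcomes for days 180 to 360. The UPIRTSO section requires prompt reporting of local deaths with no 28-day limit. This also stands, and it is why the uncovered time must not be read as events lost. It does not close the gap. Nothing says that an event found at a surveillance contact is entered as an SAE after day 28, and the SAE definition includes disability and medically important events that those questions may not bring out.

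A third reply concerns importance. The primary outcome, the sample size and the immunogenicity analyses are untouched. Both arms are injected on the same days and assessors are blinded, so a rule applied consistently would shorten the period equally in both. That is right, and it limits the severity.

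**Conclusion.** The article contradicts itself on how long SAEs are collected, and its SAE outcome fits only one of the two rules. Under the 28-day rule, 56 to 58 of 360 days (about 16%) are covered, about 84% of the outcome's calendar period lies outside formal collection, and the day 1–360 percentage would be an undercount. This depends on the 28-day rule being the one applied; under the other rule nothing is lost. It is an internal inconsistency of moderate severity in one secondary safety outcome.

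A reader might infer two stronger points that the document does not support:

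- **That 84% of SAEs would be missed.** The figure is calendar time under one of two conflicting rules. Turning it into events needs a constant SAE rate, which is an assumption, and it ignores the other routes by which hospitalisations and deaths could come to light. It is an upper-bound illustration.
- **That starting at day 1 dilutes a booster-versus-control comparison, because the groups receive the same vaccine until day 180.** The SAE item states no between-group comparison. The healthcare-utilisation and mortality items do, and they already start at day 180. Reporting SAEs from first exposure is legitimate and does not prevent a later-period table.

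**What to change.** State one SAE collection window and use it in the Fig. 2 text, the Safety monitoring plan, Safety assessment methods and Secondary outcomes. Bring the safety contact in Participant withdrawal into line with it. Either route resolves the contradiction:

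- **Collection to day 360:** amend the two 28-day statements and the withdrawal wording, and say that SAEs found at the 2-weekly contacts are recorded as SAEs. The outcome then stands as written.
- **28-day windows kept:** amend Safety assessment methods and relabel the SAE outcome as events within 28 days of each vaccination, so that it is not read as a one-year figure.

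The cost is mainly protocol wording. The first route adds little data collection, because the contacts to day 360 are already planned and already ask about hospitalisations. Recruitment began in May 2016, so the sponsor should also record which rule sites have been following. A separate table of SAEs from day 180 to day 360 is optional.

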### Randomisation

A web-based, computer-generated randomisation code will assign participants using a random permuted block method. Allocation will be stratified by age (65 years or under to 74 years, 75 years or older). Age is a significant predictor of response to vaccination, and the proportion of participants recruited who are older than 75 years may be small.

### Blinding

To minimise the potential for unintentional bias an observer-blind procedure will be followed. The participant, investigators, study staff members, and laboratory personnel will all be blinded to group assignment. One or more unblinded vaccine administrators will perform randomisation and will be responsible for both preparing and administering the blinded vaccine. This person will not be authorised to collect any safety data or to perform any other study procedures. This person will not provide any information about the contents of the syringe to study participants or personnel, and will not allow anyone to see the content of the syringe. Blinded study personnel will not be present during product preparation and administration. The vaccine will be administered in a private setting with no observers present. Contents of the syringe will be masked with an opaque tape to ensure participant blinding to group allocation. The unblinded staff will ensure that vaccination documents revealing participant group assignment are stored in a secure place to which only they have access.

### Unblinding procedures

The vaccine blind will be broken by the investigator in the event of an SAE if identification of the vaccine received could influence treatment of the SAE, or in the event of death or a life-threatening SAE where the investigator’s causality assessment is ‘related’ to the trial product. Vaccine blind will also be broken at the request of the health authority in the event of an SAE. Code-breaking will be limited, when possible, to the participant(s) experiencing the SAE. Any intentional or unintentional code breaking will be reported to the Domain Specific Review Boards (DSRB).

### Potential risks

As with any vaccination, participants may experience pain, swelling, redness or itching at the injection site. Rarely, a participant may experience an allergic reaction which produces rash, urticaria or difficulty breathing. Serious allergic reactions that can be life-threatening may occur. The incidence of severe adverse reactions are low with the trial vaccines. An increased risk of SAEs has not been reported from studies of repeated vaccination at 1 year or earlier. The risk of nonsevere local and systemic adverse reactions may be increased with repeated vaccination as a result of increased reactogenicity from pre-existing immunity. Blood taking is a common medical procedure with very low risk of complications, such as prolonged bleeding or infection, when standard procedures are followed. Risks of breaches in trial participant confidentiality will be ameliorated by following the Singapore Guideline for Good Clinical Practice (SGGCP) and the DSRB-approved study protocol.

### Potential benefits

There is a possibility that the booster vaccine administered in the experimental arm will prevent an influenza infection that might otherwise have occurred. There is also a possibility that the vaccine administered in the control arm will prevent a tetanus, diphtheria or pertussis episode that might otherwise have occurred. Participants will not be paid for participation in this study, but will be reimbursed for their time and travel costs.

### Study population

Two hundred participants will be enrolled (approximately 100 per group). The study population will be drawn from people attending outpatient services at Tan Tock Seng Hospital, Singapore and healthy volunteers from senior activity centres and community clubs in Singapore. There are no participant restrictions based on sex or race. A complete review of the inclusion and exclusion criteria for eligibility will be performed. This will entail a face-to-face interview with the potential participant and screening of electronic medical records. The potential participant will be provided with information about the trial and written informed consent obtained. No procedure or treatment associated with the study will be performed before obtaining written informed consent.

### Inclusion criteria

Participants must meet all of the inclusion criteria to participate in this study:Age 65 years or older on the day of inclusionNo influenza vaccination in the previous 10 monthsNo tetanus, diphtheria or pertussis vaccine in the previous 1 yearNo virologically confirmed influenza infection in the previous 10 monthsParticipant able to provide written informed consentAble to attend all scheduled visits and comply with all trial procedures

### Exclusion criteria

Participants meeting any of the exclusion criteria at baseline will be excluded from participation:Participation in the 4 weeks preceding the first trial vaccination or participation during the present trial period in another trial investigating a vaccine, drug, medical device, or medical procedureHistory of a life-threatening reaction to the vaccine used in the trial, or to a vaccine containing any of the same substancesKnown systemic hypersensitivity to any of the vaccine components, including:Egg protein (eggs or egg products)Chicken productsFormaldehydeNeomycin or kanamycinOctoxinol 9 (Triton X-100)Cetyltrimethylammonium bromide (CTAB)Thiomersal
History of Guillain-Barré syndrome (GBS) within 6 weeks following previous influenza vaccinationAcute respiratory infection (ARI) on the day of enrolmentModerate or severe acute illness/infection (according to investigator judgement) on the day of vaccination, or febrile illness (temperature ≥37.5 °C). A prospective participant should not be included in the study until the condition has resolved or the febrile event has subsidedSelf-reported thrombocytopenia, contraindicating intramuscular (IM) vaccinationKnown or suspected congenital or acquired immunodeficiency; or receipt of immunosuppressive therapy, such as anticancer chemotherapy or radiation therapy, within the preceding 6 months; or long-term systemic corticosteroid therapy (prednisolone ≥7.5 mg/day or equivalent for more than two consecutive weeks within the past 3 months)Chronic illness that, in the opinion of the investigator, is at a stage where it might interfere with trial conduct or completionDeprivation of freedom by an administrative or court order, or in an emergency setting, or hospitalised involuntarilyCurrent alcohol abuse or drug addiction that might interfere with the ability to comply with trial procedures in the opinion of the investigatorWomen of childbearing age will be excluded from the trial

